# ABSTRACT

| **Study Title** | Induction Chemotherapy Followed by Camrelizumab, Apatinib plus Chemotherapy as First-line Treatment for Extensive-stage Small-cell Lung Cancer: A Multicenter Single-arm Study with Biomarker Analysis |
| --- | --- |
| **Version No.** | 1.2 |
| **The Primary Clinical Research Center** | The First Affiliated Hospital of Guangzhou Medical University, Guangzhou, China |
| **The Primary Investigator** | [name] |
| **Participating Study Sites** | Zhujiang Hospital affiliated to Southern Medical University |
| **Trial Design** | Prospective, phase II clinical trial |
| **Participants** | Patients with extensive-stage small cell lung cancer who did not receive systemic treatment |
| **Study Objectives** | To evaluate the safety and efficacy of chemotherapy combined with PD-1 antibody camrelizumab and apatinib in the first-line treatment of extensive stage small cell lung. |
| **Study Endpoints** | **Key endpoints**   - Safety (per CTCAE 5.0 criteria)   **Secondary endpoints**   - Disease control rate (DCR) - Duration of response (DoR) - Objective response rate(ORR per RECIST v1.1) - Progression-Free Survival (PFS per RECIST v1.1) - Overall surviral(OS)   **Exploratory endpoint**   - Exploratory analysis（tumor mutation burden (TMB), gene mutation, homologous recombination deficiency (HRD) score and immune cells） |
| **Study Drug** | Camrelizumab、apatinib、Etoposide、Carboplatin |
| **Inclusion Criteria** | 1. Pathologically confirmed extensive stage small cell lung cancer; 2. Extensive small cell lung cancer (per the Veterans Administration 3. Lung Study Group (VALG) staging system) not receiving systemic treatment; 4. Received prior surgery and adjuvant therapy for curative intent such as radiotherapy and chemotherapy; at least 6 months of treatment-free period since last chemotherapy, radiotherapy, or chemoradiotherapy to diagnosis of extensive-stage SCLC; 5. Measurable lesions according to Response Evaluation Criteria in Solid Tumors (RECIST) version 1.1; 6. Male or female ≥ 18 years of age and ≤ 75 years of age; 7. ECOG performance status score of 0-1; 8. Life expectancy ≥ 12 weeks; 9. Adequate organ system function (excluding the use of any blood components and cell growth factors during screening):    1. Hemoglobin ≥ 9 g/dL    2. Absolute neutrophil count ≥1.5×109/L    3. Platelets ≥100 × 109/L    4. Serum albumin ≥ 3/dL    5. Total bilirubin ≤ ULN    6. ALT and AST ≤ 1.5 × ULN; AKP ≤ 2.5 × ULN    7. Serum creatinine ≤1.5 ULN or creatinine clearance(CrCl) ≥60 mL/min (Cockcroft -Gault formula). Negative urine protein or 24-hour urine protein quantification <1.0 g    8. Thyroid stimulating hormone (TSH) ≤ULN (subjects with normal T3 and T4 levels are allowed to be enrolled although TSH＞ULN) 10. Contraception (e.g., IUD, contraceptives, or condoms); a negative pregnancy test within 7 days prior to enrollment for women of childbearing age; 11. Subjects voluntarily enrolled in this study and signed an informed consent form. |
| **Exclusion Criteria** | 1. Prior treatment with apatinib, anti-programmed cell death (PD)-1, anti-PD-1, or other immunotherapy against PD-1/PD- L1; 2. Carcinomatous meningitis, subjects with asymptomatic brain metastases and did not require immediate radiotherapy could be included in the study; 3. Other malignancies diagnosed and/or treated within 5 years prior to enrollment, except cured basal cell carcinoma of the skin and carcinoma in situ of the uterine cervix; 4. There are a variety of factors that affect the oral administration of medications, such as inability to swallow, posterior gastrointestinal resection, chronic diarrhea, intestinal obstruction, etc.; 5. Have an uncontrollable pleural effusion, pericardial effusion, or ascites that cannot be controlled by drainage or other procedures; 6. Subjects with spinal cord compression that has not been cured or resolved by surgery and/or radiotherapy, or patients with spinal cord compression diagnosed after treatment, who do not have clinical evidence of disease stabilization ≥1 week prior to enrollment; 7. Subjects with hypertension that is not well controlled with oral antihypertensive medication (systolic blood pressure > 140 mmHg, diastolic blood pressure >90 mmHg), with Grade I or greater myocardial ischemia or myocardial infarction, Grade I or greater arrhythmia (including QT interval ≥440 ms) or cardiac insufficiency; 8. Subjects with signs of bleeding or predisposition to bleeding, regardless of the degree of bleeding, within 2 months prior to the first dose; history of hemoptysis (defined as more than 2.5 ml of bright red blood) or unhealed wounds, ulcers, or fractures in the previous 2 weeks; 9. Incomplete recovery from adverse events due to prior therapy, except for alopecia which did not recover to grade ≤1; 10. Major surgery or significant traumatic injury within 28 days prior to enrollment; 11. An arterial or venous thromboembolic event within 6 months, such as transient ischemic attack, deep vein thrombosis, pulmonary embolism, and other cerebrovascular accidents; 12. Those with a history of substance abuse, inability to quit, or a mental disorder; 13. Suffering from a serious and/or uncontrollable illness; 14. Vaccination or attenuated vaccine within 4 weeks prior to the first injection; 15. Known allergy to the study drugs or excipients, history of severe allergic reaction to any monoclonal antibody; history of allergy to carboplatin or etoposide ; 16. Active autoimmune disease requiring systemic therapy within 2 years prior to first dose; 17. Immunosuppressive, systemic or local absorbable hormones (prednisone or other therapeutic hormones at doses > 10 mg/day) were administered to the patient. Immunosuppressive therapy was administered and continued for 2 weeks after the first dose; 18. Participation in a clinical trial of another anticancer drug within 4 weeks; 19. In the judgment of the investigator, there are other factors that may have led to the termination of the study. |
| **Withdrawal Criteria** | - Subjects withdrew informed consent. - Progression of the disease on imaging. - Those who cannot tolerate toxicity. - Subjects missed visits or had positive blood HCG. - Other situations where the investigator felt it necessary to withdraw from the study. |
| **Termination Criteria** | - Unintended or unacceptable risks to the subject are identified. - The study drug/trial treatment is ineffective, or it is pointless to continue the trial. - For reasons such as difficulties in subject enrollment or frequent protocol deviations, the investigator decided to terminate the study. |
| **Treatment Regimen and Dosage** | 1. **Induction treatment stage: chemotherapy induction 2 cycles,** **q3w**  - Etoposide: 100 mg/m2 IV Day 1-3; - Carboplatin: AUC 5 mg/mL/min IV Day 1  1. **Combination treatment stage: chemotherapy + immunotherapy + antivascular therapy 2-4 cycles, q3w**  - Etoposide: 100 mg/m2 IV Day 1-3 - Carboplatin: AUC 5 mg/mL/min IV Day 1 - Camrelizumab: 200 mg IV Day 1 - Apatinib: 250 mg PO QD  1. **Maintenance treatment stage: immunotherapy + antivascular therapy, q3w**  - Camrelizumab: 200mg IV Day 1 - Apatinib: 250mg PO QD |
| **Study Plan** | 2020.9 - 2021.1 Submissions, Ethical Review of Research Units.  2021.2-2022.2 The patients were enrolled and the data were recorded.  2022.3-2023.03 Complete follow-up and data collection of all enrolled patients.  2023.04-2024.12 Data analysis, paper writing and contributions. |

# SCHEDULE OF ACTIVITIES

| **Stage** | **Screening Period** | | **Treatment Period**  **(21 days/cycle)** | | **End of Treatment**  D1±3 | **Safety Follow-up**  (30 days) | **Survival Follow-up**  Every 3 months |  |
| --- | --- | --- | --- | --- | --- | --- | --- | --- |
|  | -28-1 days | -7-1 days | Cycle 1  D1±3 | Follow-up cycle  D1±3 |  |  |  |  |
| Baseline | | | |  |  |  | |  |
| Written Informed Consent Form | X |  |  |  |  |  |  |  |
| Inclusion/Exclusion Criteria | X |  |  |  |  |  |  |  |
| Demographics/Medical History/Previous Medication | X |  |  |  |  |  |  |  |
| Vital Signs | X |  |  | X | X | X |  |  |
| Weight, height | X |  |  | X | X | X |  |  |
| Physical Examination | X |  |  | X | X | X |  |  |
| ECOG PS Sore | X |  |  | X | X | X |  |  |
| Laboratory Tests | | | |  |  |  | |  |
| 12-lead ECG | X |  | X | X | X | X |  |  |
| Hematology/Blood Biochemistry Urinalysis/Urine  Routine/Stool Tests |  | X |  | X | X | X |  |  |
| Coagulation Function |  | X |  | X | X | X |  |  |
| Pregnancy Test |  | X |  |  | X |  |  |  |
| Thyroid Function | X |  |  | X | X |  |  |  |
| Myocardial Enzyme Profile |  | X |  | Add when clinically indicated | | |  |  |
| Pituitary Function Tests | X |  |  | Add when clinically indicated | | |  |  |
| HIV,, , HBV and HCV Tests | X |  |  |  |  |  |  |  |
| Echocardiography |  | X |  | Add when clinically indicated | | |  |  |
| Pulmonary Function Tests and Arterial Blood Gas (ABG) Analysis | X |  |  | Add when clinically indicated | | |  |  |
| Medication |  |  | 1-2 cycles of induction treatment chemotherapy, 3-4 cycles of combination treatment , and follow by maitanence treatment. | |  | |  |  |
| AE Assessment | X |  |  | X | X | X |  |  |
| Concurrent Medications | X |  | X | X | X | X |  |  |
| After-Treatment Visits | | | |  |  |  | |  |
| Survival Follow-up |  |  |  |  |  | X | X |  |
| Anti-Tumor Therapy |  |  |  |  |  | X | X |  |
| Evaluation of Efficacy | | | |  |  |  | |  |
| Imaging Evaluation | X |  | Assess on day 21 of cycle 1, and every 6 weeks thereafter until disease progression or the start of a new treatment. | | X |  |  | |

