# STUDY DESIGN

## Schematic Design

This study is a prospective, multi-cohort clinical trial designed to evaluate the safety and efficacy of chemotherapy(Etoposide + Carboplatin) in combination with the PD-1 antibody camrelizumab and the anti-angiogenic drug apatinib in the treatment of patients with extensive stage small cell lung cancer.

Study objectives: To explore the safety of induction chemotherapy followed by chemotherapy combined with immune and anti-angiogenic drugs for the first-line treatment of patients with ES-SCLC; (2) To explore the efficacy of induction chemotherapy followed by chemotherapy combined with immune and anti-angiogenic drugs for the first-line treatment of patients with ES-SCLC; (3) To explore the precision treatment population of patients with extensive small cell lung cancer treated with chemotherapy combined with immunological and anti-angiogenic agents after induction chemotherapy.

If subjects did not withdraw consent from the trial or were deemed by the investigator to be unsuitable for further trials, and each subject will be treated until disease progression or, drug-induced toxicities are intolerable, followed by a survival follow-up period.

[figure not shown]
(1) Etoposide: 100 mg/m2 IV Day 1-3; Carboplatin: AUC 5 mg/mL/min IV Day 1; Camrelizumab: 200 mg IV Day 1; Apatinib: 250 mg Po QD.

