# TRETAMENT REGIMEN AND DOSAGE

1. **Induction treatment stage: chemotherapy induction 2 cycles, q3w**

- Etoposide: 100 mg/m2 IV Day 1-3;
- Carboplatin: AUC 5 mg/mL/min IV Day 1

1. **Combination treatment stage: chemotherapy + immunotherapy + antivascular therapy 2-4 cycles, q3w**

- Etoposide: 100 mg/m2 IV Day 1-3
- Carboplatin: AUC 5 mg/mL/min IV Day 1
- Camrelizumab: 200 mg IV Day 1
- Apatinib: 250 mg PO QD

1. **Maintenance treatment stage: immunotherapy + antivascular therapy, q3w**

- Camrelizumab: 200mg IV Day 1
- Apatinib: 250mg PO QD

The treatment was administered in 3-week cycles until PD, intolerable toxicity, death, patient withdrawal of information, or discontinuation in the evaluation of the investigator.

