### Physical examination

A complete physical examination includes: general condition, respiratory, cardiovascular, abdominal, skin, head and neck (including ears, eyes, nose, and throat), lymph nodes, thyroid, musculoskeletal (including spine and extremities), genital/anal, and neurologic evaluation.

1. **12-lead electrocardiogram**

Resting 12-lead ECGs will be analyzed at a local laboratory according to the visit schedule. A 12-lead ECG should be performed in each case after the subject has rested in the prone position for at least 5 minutes, and further ECGs will be performed when clinically indicated cardiac-related event. The investigator completes the ECG assessment on the day of the examination and records the results on the ECG. The same assessment should be used throughout the study.

ECGs will be recorded at 25 mm/sec. The investigator should evaluate all ECGs according to the category of clinically significant abnormality/non-clinically significant abnormality; if there is a clinically significant abnormality results, the investigator should document the result as an AE in the CRF.

1. **Vital signs**

Vital signs will be checked as described in the study visit schedule. Vital signs include temperature, pulse rate, respiratory rate and blood pressure.

Additional vital sign assessment monitoring may be performed at the discretion of the investigator in accordance with standard clinical practice or based on clinical need.

In the presence of AE/SAE, additional recorded vital sign values may be taken on the CRF (if applicable).Record the date and time of collection and measurement in the appropriate section.

- 1. **Pulse and blood pressure**

Pulse and blood pressure were taken during the Screening Period and prior to the planned administration of the daily infusion of Camrelizumab.

Blood pressure monitoring: For each blood pressure measurement, no smoking or coffee for 30 minutes prior to the measurement and rest quietly for at least 10 minutes.

Minutes were taken in a sitting position with the elbow placed at the same level as the heart, and each blood pressure measurement was taken on the same side.

Blood pressure was measured by the investigator during the screening period and prior to each scheduled administration of camrelizumab; during the study, blood pressure monitoring was done by the subjects themselves and recorded on subject diary cards, and blood pressure was measured weekly for the first 2 cycles.

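### The Schedule of Activities and Section 8 disagree on the number of induction and combination cycles, and under Section 8 the only stated weekly blood-pressure window ends before apatinib starts

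*Protocol*

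**What the plan says.** Section 8 of the protocol defines the first stage as "Induction treatment stage: chemotherapy induction 2 cycles, q3w", with etoposide and carboplatin only, and the second as "Combination treatment stage: chemotherapy + immunotherapy + antivascular therapy 2-4 cycles, q3w", in which camrelizumab and apatinib are added. Maintenance with the latter two drugs follows. The Abstract agrees, giving the second stage as "chemotherapy + immunotherapy + antivascular therapy 2-4 cycles, q3w". Section 3.1 states the same order in its objectives: "induction chemotherapy followed by chemotherapy combined with immune and anti-angiogenic drugs".

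The Medication row of the Schedule of Activities reads differently: "1-2 cycles of induction treatment chemotherapy, 3-4 cycles of combination treatment", followed by maintenance. The Schedule sets the cycle length at 21 days.

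Table 8 (Section 11.2) has columns for Cycle 1, Cycle 2 and the Nth cycle. Each of the four drugs has a single entry with no stage and no starting cycle, and each entry carries a note pointing to Section 8.

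On blood pressure, Section 13.1.2 sets one weekly frequency: "blood pressure was measured weekly for the first 2 cycles". It also has subjects keep their own readings on diary cards while on study, with no other frequency given for them. The investigator's readings are tied to screening and to camrelizumab dosing. The Schedule also marks vital signs, which include blood pressure, at the follow-up cycles.

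**The concern.** Giving induction chemotherapy before the immune and anti-angiogenic drugs is what defines this trial. It is in the title and the objectives. The Background gives a safety reason: tumour involvement of large vessels may raise the bleeding risk of anti-vascular treatment, which prompts the question whether that involvement can be reduced. The number of induction cycles before apatinib is therefore a core design parameter, and the protocol gives it in two versions.

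The primary endpoint is safety, in a planned 36 subjects. If sites work from different pages, subjects could begin the combination in different cycles, or receive different numbers of combination cycles, and still be pooled as one regimen. The starting cycle also decides which adverse events arose during the combination and which during chemotherapy alone.

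The blood-pressure window matters because the protocol itself treats hypertension as a risk. Section 5.2 excludes poorly controlled hypertension, and Table 3 lists hypertensive crisis among the reactions needing special attention with apatinib. Weekly readings confined to a stage without apatinib would say little about blood pressure on that drug.

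**Working it through.** No sample-size or power formula is involved. The check lists what each place allows and converts it to study days.

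**Inputs**
- Cycle length: 21 days (Schedule of Activities).
- Section 8 and Abstract: induction 2 cycles, combination 2 to 4.
- Schedule, Medication row: 1-2 for induction, 3-4 for combination. This can be read as counts of cycles or as cycle numbers.
- Weekly blood-pressure window: the first two cycles (Section 13.1.2).

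**Formulas**
- First day of camrelizumab and apatinib = 21 × (induction cycles) + 1.
- Total chemotherapy cycles = induction + combination.
- Apatinib cycles inside the window = 2 − (induction cycles), not below 0.

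**Section 8 and Abstract**
- Start: 21 × 2 + 1 = day 43, the first day of cycle 3.
- Total: 2 + 2 = 4 up to 2 + 4 = 6 cycles.

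**Schedule read as counts**
- Start: 21 × 1 + 1 = day 22, or 21 × 2 + 1 = day 43.
- Total: 1 + 3 = 4 up to 2 + 4 = 6 cycles, the same range as Section 8.
- Pairs (induction, combination) allowed by both: (2,3) and (2,4).
- Allowed by Section 8 only: (2,2).
- Allowed by the Schedule only: (1,3) and (1,4).
- Spread in start: 43 − 22 = 21 days, one cycle.

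**Schedule read as cycle numbers** (cycles 1-2, then cycles 3-4)
- Start: day 43, as in Section 8.
- Combination: exactly 2 cycles, total 4. Cycles 5 and 6, which are Section 8's third and fourth combination cycles, are not shown.

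**Blood-pressure window**

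Two cycles are 2 × 21 = 42 days, so the window is days 1 to 42.

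| Source and reading | Combination starts | Combination cycles | Apatinib cycles inside days 1-42 |
| --- | --- | --- | --- |
| Section 8 / Abstract | day 43 | 2 to 4 | 2 − 2 = 0 |
| Schedule, counts | day 22 or 43 | 3 or 4 | 2 − 1 = 1, or 2 − 2 = 0 |
| Schedule, cycle numbers | day 43 | 2 | 2 − 2 = 0 |

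Neither reading of the Schedule row reproduces Section 8. Under Section 8 the window closes on day 42 and apatinib begins on day 43, so they do not overlap.

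Days are nominal: they ignore the ±3-day visit window and any treatment delay.

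**The case against.** The dosing text is consistent. Section 8 and the Abstract match, and Section 3.1 states the same order. The wording of the Schedule row suggests that cycle numbers may have been meant, in which case there is no conflict over the start. This stands in part: a day-22 start arises only under the count reading, and under that reading the total of 4 to 6 chemotherapy cycles agrees with Section 8. But the cycle-number reading leaves its own conflict over the length of the combination stage, so the row needs correcting either way.

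A reader might infer from Table 8 that camrelizumab and apatinib start on day 1, which would widen the spread to 43 − 1 = 42 days. The documents do not support this. Every drug entry in Table 8 refers to Section 8 and none names a starting cycle. Taken literally, the table would also continue carboplatin and etoposide in every cycle, against the maintenance stage in Section 8. It is best read as a list of doses whose layout omits the stages: a secondary ambiguity.

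A reader might also infer that blood pressure goes unmonitored on apatinib, or that hypertension events would be missed. That is not so. Diary self-monitoring runs during the study, the investigator measures before each camrelizumab dose, vital signs are marked at follow-up cycles, and adverse events are collected until 30 days after the last dose. What is missing is a stated diary frequency after the second cycle.

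Finally, the first two cycles might have been meant as the first two cycles on apatinib, which would close the gap. The text does not say so.

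**Conclusion.** The conflict over cycle counts is established. The Schedule's Medication row disagrees with Section 8 and the Abstract under both readings: by up to 21 days in the start of camrelizumab and apatinib, and by the loss of a two-cycle combination stage, if it gives counts; by the loss of the third and fourth combination cycles if it gives cycle numbers. This conclusion does not depend on Table 8.

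The blood-pressure point is conditional. If Section 8 governs and the window means study cycles 1 and 2, the only stated weekly frequency falls entirely before apatinib, with zero weeks of overlap. If a single induction cycle were given, as the count reading permits, the overlap would be one cycle, or three weeks.

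The point should be corrected because the order of treatment defines the trial and safety is its primary endpoint. The documents do not show that any subject was treated differently because of it, and this review takes no view on which schedule is right.

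**What to change.** Reconcile the Abstract, the Medication row of the Schedule of Activities, Section 8 and Table 8 to a single statement of the number of induction cycles, the number of combination cycles, and the cycle in which camrelizumab and apatinib begin. The Schedule row should make plain whether its figures are counts or cycle numbers. Table 8 should either show the treatment stages or say that it lists doses only and that Section 8 governs timing.

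Reconcile the blood-pressure window in Section 13.1.2 with the treatment stages by expressing it by stage instead of by study cycle number, and state how often diary readings are expected outside that window. The number of cycles, the starting cycle and the monitoring frequency are for the sponsor's clinical team to decide.

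The cost is protocol wording and a small change to one table. No subjects need to be added.

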# BACKGROUND OF THE STUDY

SCLC accounts for about 15% of all lung cancers, and it can be divided into two categories: limited stage (LS-SCLC) and extensive stage (ES-SCLC)^1^ . Limited stage SCLC is confined to one side of the lung and may be present in lymph nodes on the same side of the chest. If the cancer spreads to the other side of the lung, to lymph nodes on the other side of the chest, or to distant organs, it is characterize as extensive stage. Few patients diagnosed with extensive or unresectable limited stage are cured with surgery. Regardless of the stage, systemic platinum-based chemotherapy is the mainstay of treatment for SCLC. Although SCLC is sensitive to platinum-based chemotherapy, with patients achieving remission rates of 50-90%, recurrence and rapid progression of the disease are very common^2^ .

After close to 20 years of using platinum-based chemotherapy as the standard of care, immune checkpoint inhibitors are finally making a breakthrough in SCLC treatment. Bristol-Myers Squibb's PD-1 inhibitor Opdivo (Nivolumab) received accelerated approval in August 2018 as a third-line therapy for patients with ES-SCLC. This was followed in June 2019 by Merck Sharp & Dohme's Keytruda (Pembrolizumab) was also approved for a third-line indication; two PD-L1 antibodies, Roche's Tecentriq (Atezolizumab) in March 2019 and AstraZeneca's Imfinzi (Durvalumab) in March 2020, were even more consecutively approved as first-line treatments in combination with chemotherapy for patients with ES-SCLC^3^ .

In addition, Yervoy (ipilimumab), a CTLA-4 inhibitor developed by BMS, is not FDA-approved for the treatment of SCLC, but it is included in the National Comprehensive Cancer Network (NCCN) guidelines in combination with Opdivo as a second-line therapy for the treatment of patients with SCLC who have experienced disease recurrence after first-line chemotherapy^4^ .

The two immune checkpoint inhibitors currently approved for broad-stage small cell lung cancer indications are both PD-L1 antibodies. 2020 ASCO reported updated data on two PD-1 antibodies, Nivolumab and Pembrolizumab, in first-line combination chemotherapy. The primary endpoint of PFS was achieved with Nivolumab in combination with CE versus CE chemotherapy, with a median PFS of 5.5 months versus 4.7 months, HR=0.68, p=0.047, and a statistically significant difference of 0.8-month. Unfortunately, the secondary endpoint of OS was not achieved in the modified study, with a median OS of 11.3 months versus 9.3 months ,p=0.14, which was not statistically significant. The Keynote-604 study also did not provide a positive OS result for first-line combination chemotherapy with pembrolizumab, although the median OS was 10.8 months versus 9.7 months, with a P-value of 0.0164, which did not meet the efficacy cutoff of 0.0128, and was therefore not statistically different. statistical difference^5^ .

The efficacy of PD-1 combination chemotherapy in the first-line treatment of small cell lung cancer is not satisfactory, whether immunization combined with other modalities, such as anti-angiogenic drugs, can further improve the efficacy? Impower-150 study^6^ gives a hint, the study set up three groups, the ABCP group (immunotherapy + anti-angiogenesis + chemotherapy), the ACP group (immunotherapy + chemotherapy), and the BCP group (anti-angiogenesis + chemotherapy). This study used platinum doublet chemotherapy plus bevacizumab, which has a well-established gold standard status for advanced non-squamous non-small cell lung cancer (NSCLC), as the control group (while other related studies used standard platinum doublet regimens as control). It was the first study to demonstrate that the addition of atezolizumab to the combination of bevacizumab, paclitaxel, and carboplatin was superior to the three-drug combination without immunotherapy, specifically showing a benefit for patients (ABCP group vs BCP group: Overall Survival (OS) 19.5 months vs 14.7 months). This represents the first and currently the only phase III clinical trial demonstrating statistically and clinically significant improvements in Progression-Free Survival (PFS) and OS with first-line immunotherapy combined with anti-angiogenesis for metastatic non-squamous NSCLC. There were also numerical improvements in Objective Response Rate (ORR) and Duration of Response (DOR) with the four-drug combination compared to the three-drug regimens, with ORR reaching 56% in the four-drug group compared to 40-41% in the three-drug groups, and DOR increasing from 6.0-8.3 months to 11.5 months. The incidence of new brain metastases in the ABCP and BCP groups was also lower than in the ACP group, at 7%, 6%, and 11.9%, respectively.The study results suggest that, based on the selection of appropriate patient populations, adding anti-angiogenic drugs to a chemotherapy + immunotherapy regimen may further enhance efficacy. Specifically, the ABC group (immunotherapy + anti-angiogenic + chemotherapy) in the Impower-150 study demonstrated better overall survival (OS 19.5 months vs. 14.7 months) compared to other combinations, providing a positive signal for first-line treatment of small-cell lung cancer.

Additionally, the Keynote-021 cohort study^7^ reached similar conclusions. This study evaluated the effectiveness of the combination therapy "chemotherapy + pembrolizumab + bevacizumab." Different combinations exhibited varying objective response rates (ORR), with the combination including bevacizumab showing a higher ORR (Group A 40%, Group B 56%, Group C 75%). This further supports the notion that adding anti-angiogenic drugs to immunotherapy may enhance treatment efficacy.

Furthermore, the PASSION study^8^ of camrelizumab focused on the combination therapy with apatinib for extensive-stage small-cell lung cancer. Preliminary results indicated an ORR of 34% in the overall patient population, including both chemotherapy-sensitive and chemotherapy-resistant patients, with a duration of response (DOR) of 6.2 months, progression-free survival (PFS) of 3.6 months, and overall survival (OS) of 8.4 months. This study suggests that the combination of camrelizumab and apatinib demonstrates favorable efficacy, especially in patients with small-cell lung cancer after platinum-based chemotherapy, and its safety profile is acceptable.

In addition, approximately 75%-90% of small cell lung cancer (SCLC) is centrally located, occurring within or up to one segment of the bronchi. Although the tumor originates from the bronchial mucosa, it tends to grow along the submucosa and infiltrate the surrounding interstitium along its longitudinal axis. SCLC exhibits characteristic lymphatic spread, with prominent involvement of lymph nodes. It often compresses, embeds, and invades structures in the lung hilum and mediastinum, such as the pericardium, major blood vessels, trachea, bronchi, esophagus, and nerves.

A retrospective analysis^9-10^ of 50 cases of SCLC examined the vascular involvement, categorizing it into three levels based on the degree of invasion. The results showed that out of the 42 cases with vascular involvement, there were a total of 84 affected vessels, including 37 instances of involvement of the pulmonary artery, 29 involving the pulmonary veins, 16 involving the superior vena cava, and 2 involving the aorta. Based on the degree of vascular involvement, 12 cases were classified as level 1, 3 cases as level 2, and 69 cases as level 3. Vascular involvement in SCLC, particularly in major blood vessels, may increase the risk of bleeding during anti-vascular therapy. It prompts consideration of whether interventions can be employed to reduce the extent of tumor invasion into the vessel walls, thereby enhancing the safety and efficacy of anti-vascular treatment for this population.

Small cell lung cancer is a highly malignant tumor sensitive to chemotherapy. Over the past few decades, platinum-based chemotherapy combined with etoposide has been widely accepted as the standard first-line treatment for SCLC. Objective response rates of around 60% have been achieved with this regimen, leading to tumor shrinkage in most patients. However, the development of resistance and subsequent relapse and metastasis commonly occur shortly after chemotherapy. Consequently, there is a need to explore an investigational clinical study focusing on the safety and efficacy of combining immune checkpoint inhibitors and anti-vascular agents with first-line chemotherapy after induction therapy for SCLC, aiming to gain preliminary insights into the potential benefits and safety of this combined approach.

